#### Methods: data analysis

The primary outcome for this sub-study will be intentions to take up screening in 3 years in women assessed 6 months after being told that they are at low risk and receive the recommendation to delay attending screening. Our main focus will be on estimating the proportion of women intending to take up screening, but we will also formally compare this proportion with women who receive provision of “below average risk” breast cancer risk estimates (< 2%) but no screening recommendations, recruited over the previous 12 months of BC-Predict. Intention to attend screening is a consistent predictor of subsequent screening attendance (*r* = + 0.42 in a systematic review that identified k = 19 such tests) [58].

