All BC-Predict participants will have been invited for breast screening but a proportion may choose not to attend their breast screening appointment; attendance at breast screening mammogram is not a compulsory part of the study. The Participant Information Sheet explains that participants’ mammographic breast density will be included in their risk assessment, providing they attend their mammogram within 6-weeks of their first offered appointment. It is also explained that including mammographic density increases accuracy of the risk assessment. Any participant who declines a mammogram or has a mammogram after this time will not have this data included in their risk assessment, which is explained in their risk feedback letter.

To assess self-reported harms and benefits, and to inform an economic analysis, a randomly selected subsample of *n* = 2108 women (*n* = 1054 each from usual care NHSBSP and BC-Predict) will be asked to complete questionnaires assessing psychological benefits and harms of BC-Predict at baseline, 3-months and 6-months. For women in both groups, the request to complete the questionnaire will be sent shortly after their mammography invitation but before their first offered mammogram appointment, asking for their help in evaluating a new approach to providing NHS breast screening. They will be given instructions to complete an online consent form and questionnaire using their unique study identification number on SmartSurvey (https://www.smartsurvey.co.uk/). The same women will be asked to complete the questionnaire three and 6 months after their first offered mammogram appointment. Women in both experimental groups will only receive follow-up questionnaires once they receive a clear mammogram result.

The risk assessment and feedback will take account of each patients’ journey through the NHSBSP. The study team will periodically check screening outcomes for participants. There are a number of initial screening outcomes: (a) clear mammogram and woman will be invited for routine breast screening in three-years (routine recall); (b) mammogram taken is technically inadequate so repeat mammogram is required (technical recall); (c): suspicious mammogram and further assessment required (recall for assessment). For all scenarios the GP will be informed of the participant’s involvement in the study and provided with their risk feedback.

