### Sub-study three: assessing feasibility of increasing screening interval for women at low risk

#### Objectives

To evaluate the impact of providing materials for women at low risk explaining that less frequent screening may provide a better balance of benefits and harms for them.

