#### Methods: design, sample, recruitment and data collection

In the final 4 months of the 16-month period of implementation of risk estimation, we will extend the offer of risk provision to include information about how, for women at low risk of breast cancer delaying further NHSBSP for a further period of 5 years may provide a better balance of benefits and harms for them. This information will be presented to all women in East Lancashire and Oldham as part of the invitation process, and repeated for women at low risk (< 1.5% over 10 years) as part of their risk feedback letter and accompanying leaflet. Every woman identified as being at low risk will be asked to complete the online questionnaire assessing harms and benefits of BC-Predict at 6 months, in contrast to the main BC-Predict study, where only a sub-sample will be asked to complete this questionnaire.

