#### A decision analytic model-based economic analysis

A decision analytic-model based economic analysis will be used to understand the potential relative cost-effectiveness of using a modified screening interval for women identified to be at low-risk of breast cancer as part of a stratified-BSP compared with the current NHSBSP. This analysis will build on an early economic analysis we previously conducted [11]. The model will be populated with data from the published literature and the current study to understand the relative costs and benefits of the modified screening interval for low-risk women assuming the perspective of the NHS and the impact on QALYs over the lifetime horizon for the defined population of women eligible for NHSBSP. Extensive sensitivity analysis will be used to understand the key drivers of relative cost-effectiveness when implementing a modified screening interval for low-risk women.

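### Sub-study three's primary outcome, intention to attend at 3 years, does not by itself separate women who would delay as advised and return from women who would not attend again

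*Protocol article*

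**What the plan says.** The objective of sub-study three concerns screening less often, not stopping: "To evaluate the impact of providing materials for women at low risk explaining that less frequent screening may provide a better balance".

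Under its design heading, the message for low-risk women (10-year risk below 1.5%) is that "delaying further NHSBSP for a further period of 5 years may provide a better balance of benefits and harms for them". It is given to all women invited in East Lancashire and Oldham in the final 4 months, and repeated in the risk letter and leaflet for those found to be at low risk. The data analysis section describes these women as those who "receive the recommendation to delay attending screening".

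The outcome is then fixed: "The primary outcome for this sub-study will be intentions to take up screening in 3 years in women assessed 6 months after being told". The summary is a single proportion: "Our main focus will be on estimating the proportion of women intending to take up screening". It will also be compared with women recruited earlier who received "breast cancer risk estimates (< 2%) but no screening recommendations".

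Three years is the routine interval. The main Procedure section describes the ordinary outcome as "clear mammogram and woman will be invited for routine breast screening in three-years (routine recall".

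The economic section of the sub-study aims "to understand the potential relative cost-effectiveness of using a modified screening interval for women identified to be at low-risk", using published data and data from the current study.

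**The concern.** The advice and the outcome refer to different points in time. A longer interval works as intended if women accept missing the 3-year screen and then attend the later one. The primary outcome addresses the first step only. A woman who says no at 3 years may be following the advice exactly, or may have decided not to be screened again, and she is scored the same either way.

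This matters because the protocol treats lower attendance as a potential harm. Its list of harms includes lower uptake of the screening programme, and the Discussion raises false reassurance from low-risk results. In this sub-study a lower 3-year intention is also what following the recommendation would look like. The same movement in the primary outcome could therefore be the intended effect, a harm, or a mixture. Return at the later screen is also a natural input to a model of a modified interval, and the primary outcome cannot supply it.

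**Working it through.** No sample size, power or error rate is stated for sub-study three, so there is no figure to reproduce. The check sets the stated items side by side and asks what the outcome identifies.

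**Inputs**
- Interval in the message: a 5-year delay (sub-study three, design section).
- Horizon of the primary outcome: 3 years, asked 6 months after the letter (sub-study three, data analysis).
- Usual recall: 3 years (main Procedure section).
- Comparator: below-average-risk women with no delay recommendation (sub-study three, data analysis).
- Other intention measure: Table 1 lists intention for future screening at all three timepoints, with no horizon given.
- Other information on delay: up to 12 interviews 1 month after the letter (sub-study three, qualitative process analysis).

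**What the outcome identifies**
1. Let p be the share of low-risk women intending to attend at 3 years, and q = 1 − p the share not intending to.
2. Split q into a, who would delay and attend the later screen, and g, who would attend neither: q = a + g.
3. The primary outcome gives p, and hence q. It gives no second equation for a or g.
4. From that outcome alone, 0 ≤ g ≤ q. A larger sample estimates q more precisely but does not narrow the range for g within it.
5. The comparison with below-average-risk women gives the difference in q between the two groups. It does not say how the difference divides between a and g.

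**Whether something else in the document supplies the split**
- The Table 1 intention item might, if its wording covers a later screen. The article does not say.
- Attitudes to screening and knowledge are collected at 6 months and are informative, but neither is an intention to attend at a given date.
- The interviews cover women's thinking about delay. With at most 12 purposively chosen women, they cannot estimate a proportion.

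No section of the article names an intention item at 5 years or at the end of the delay, and the stated primary outcome and main focus use none.

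**The case against.** The strongest reply is that 3 years is the right horizon for the question the protocol asks. The background to the sub-study stresses reluctance to give up screening: strong public belief in screening, a sense of being denied a service, and possible worry. Whether women would still want the usual 3-year screen tests that directly. It is also the only natural common horizon with a comparison group that was given no advice to delay. This stands, and it is why the 3-year item should stay. The outcome is incomplete, not wrong.

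A second reply is that this is a condensed article. The questionnaire is not shown, and the Table 1 intention item has no horizon. This stands too. A reader might infer that nothing in the study could tell delay from disengagement; the document does not support that, and the point is confined to the primary outcome as stated.

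A third reply is that the consequences are presumed. A reader might infer that the investigators will take any fall in 3-year intention as acceptance of the longer interval, or that the economic model will rely on this outcome for return rates. The data analysis section sets no success threshold and does not say how a fall will be interpreted. The economic section draws on the literature as well as the study and plans extensive sensitivity analysis, in which later attendance could be varied. What remains is that the stated outcome leaves the interpretation open, when one further question could settle much of it.

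**Conclusion.** The point holds in a limited form. Sub-study three recommends a 5-year delay but fixes its primary outcome as one proportion intending to attend at 3 years. That proportion measures willingness to forgo the usual screen. Alone, it does not separate women who would delay and return from women who would not attend again.

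No numerical size can be given: the document reports no expected 3-year intention among low-risk women, and the argument depends on no count or response rate. The gap is structural. From the primary outcome alone, the share disengaging lies between zero and the whole share not intending at 3 years.

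The conclusion rests on two readings: that the outcome is analysed as the single proportion described, and that no later-horizon item exists beyond what the article names. If the full questionnaire already holds such an item, the remaining point is only that its result should be reported with the primary outcome. This is a worthwhile, inexpensive improvement and does not invalidate the sub-study. It implies no view on which screening interval is appropriate.

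**What to change.** Keep the 3-year intention item as it is for the comparison with below-average-risk women.

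Check whether the low-risk women's 6-month questionnaire already asks about the later screen. If not, add one intention item about the screen at the end of the delay described in their letter, with the same response format and cut-off as the 3-year item so that the two can be cross-classified.

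Among low-risk women, report three groups:
- intends to attend at 3 years;
- does not intend to attend at 3 years but intends to attend the later screen;
- intends neither.

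State that feasibility of the longer interval will be interpreted from this split, and make the split available to the economic model.

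The cost is one more item in an online questionnaire already planned for every low-risk woman. The drawback is that the new item has no counterpart in the comparison group recruited earlier, so the split is descriptive within the advised women and the formal comparison stays on the 3-year item.

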#### Qualitative process analysis

A qualitative process analysis will be conducted in line with MRC guidance [48]. A sample of low risk women (up to *n* = 12) who had received low risk estimates will be interviewed 1 month after receiving the feedback letter. They will be sample purposively to provide variation in the three screening sites (Oldham Integrated Care Centre, Burnley General Hospital and East Lancashire mobile breast screening van). Interviews will focus on the extent to which the possibility of receiving an estimate of low risk was considered before consenting to risk estimation, the acceptability of the information communicated and particularly the recommendation to delay screening, and any deliberations about delaying screening. Data will be analysed using a manifest, inductive thematic analysis, and will involve comparison of interviews with those women told they are at below average risk, but given no particular recommendation.

#### A decision analytic model-based economic analysis

A decision analytic-model based economic analysis will be used to understand the potential relative cost-effectiveness of using a modified screening interval for women identified to be at low-risk of breast cancer as part of a stratified-BSP compared with the current NHSBSP. This analysis will build on an early economic analysis we previously conducted [11]. The model will be populated with data from the published literature and the current study to understand the relative costs and benefits of the modified screening interval for low-risk women assuming the perspective of the NHS and the impact on QALYs over the lifetime horizon for the defined population of women eligible for NHSBSP. Extensive sensitivity analysis will be used to understand the key drivers of relative cost-effectiveness when implementing a modified screening interval for low-risk women.

## Discussion

The present research aims to provide evidence on the feasibility of risk-stratified screening, by providing information about likely effects, both positive and negative, and which of these effects are likely to drive cost effectiveness. Due to the wish to avoid participant burden, some additional potential benefits and harms of screening were not examined, and merit consideration in future research.

One key issue that the present research does not cover relates to the possible benefit that risk estimation may prompt women to consider changes in their health-related behaviours to reduce cancer risk. An estimated 20–30% of breast cancer cases are thought to be attributable to excess weight, weight gain lack of physical activity (PA) and high alcohol intakes [59–61]. In general, communicating personalised risk in the absence of supportive programmes has small effects on increasing healthy lifestyle behaviours that are not maintained [62, 63]. Nevertheless, studies that have used personalised risk communication to bring about changes in health-related behaviours to date have not used additional strategies to optimise behaviour change for which there is good evidence [63]. Further, even small effects on these behaviours are achieved by communicating personalised risk information, then large population reductions in these unhealthy behaviours should follow.

The BC-Predict feedback materials include information on which behaviours are likely to reduce breast cancer risk, but the programme does not include any attempts at promoting health-related behaviour change. Women at higher breast cancer risk will have a greater proportional risk reduction through following healthy lifestyle recommendations [64, 65]. There is evidence that these women may also be more motivated to initially engage with evidence-based behaviour change programmes, maintain engagement, and thereby produce more behaviour change [66]. By contrast, it is possible that the provision of low risk results to women my produce false reassurance. This could result in women at low risk being less inclined to engage in behaviours likely to promote health although the wider evidence suggests that is not likely [67].

The present research will provide key information on feasibility of implementing risk-stratified screening into routine breast cancer screening. It complements two large ongoing trials. The WISDOM trial in the USA [68] and the MyPeBS trial in several European countries [69] are designed to show that risk-stratified screening is non-inferior to routine breast cancer screening, in terms of the number of late-stage cancers detected. In particular, the present research does not focus on effectiveness, but instead will provide information about the likely harms and benefits of risk-stratified screening, and will identify what are the key uncertainties that are likely to inform effectiveness and cost-effectiveness. It also has a more pragmatic focus than these two large ongoing trials, in considering what are the likely effects on the healthcare system when implementing risk stratification as part of routine NHSBSP, including an explicit quantitative and qualitative process analysis of the effects of this implementation.

## Data Availability

Not applicable, as protocol paper.

## Abbreviations

EVPI: Expected value of perfect information
EVPPI: Expected value of partial perfect information
FHRP: Family history, risk and prevention
NHSBSP: National health service breast screening programme
NICE: National institute for health and care excellence
PROCAS: Predicting risk of cancer at screening study
QALY: Quality-adjusted life year
SNP: Single nucleotide polymorphisms
